#### Randomization

To reduce contamination of intervention effects across participants, randomization will occur at the level of local Safety Day programs. Participating Safety Day programs will then be randomly assigned to one of the three study conditions so that individuals within the same site receive the same intervention.

#### Process and outcome measures

Program process and outcomes will be measured by surveys completed by students, instructors, and coordinators. Instruments are described below, and instrument means, standard deviations, and alpha coefficients are displayed in Table 1.

**Table 1 Tab1:** Instrument means, standard deviations, and alpha coefficients (n = 110)

Instrument Name	Number of items	Range of scores	Mean (SD)	Cronbach’s alpha
Knowledge	12	0.08-0.92	0.69 (0.18)	.71
Interpersonal Influences	1	1-4	2.45(1.17)	n/a
Use of HPDs & Strategies	6	0-1	0.67(0.27)	.69

#### Intervention effectiveness evaluation

After obtaining parental informed consent and soliciting the assent of child participants, pre- and post-intervention data will be collected from youths. Pre-test data will be collected via pencil-and-paper survey forms prior to the delivery of content. Three- and 12-month post-test data will be collected via the youth’s preferred communication medium following the booster intervention. Instrument means, standard deviations, and alpha coefficients are summarized in Table 2.

**Table 2 Tab2:** Timetable of project activities and benchmarks for success

Activity	Year 1 months						Year 2 months						Year 3 months						Year 4 months		
	1/2	3/4	5/6	7/8	9/10	11/12	13/14	15/16	17/18	19/20	21/22	23/24	25/26	27/28	29/30	31/32	33/34	35/36	37/38	39/40	41/42
Recruit, enroll & randomize 36 sites	X	X	X	X																	
Train coordinators (Groups A,B); & distribute materials (Groups A,B,C)		X	X	X	X	X															
Recruit 24 instructors; enroll youth; collect baseline data; deliver interactive program (Groups A,B)					X	X	X	X													
Distribute, collect 3-month surveys (Groups A,B)					X	X	X	X	X	X											
Distribute booster reminders (Group B)							X	X	X	X	X	X									
Collect 12-month surveys; distribute incentives (Groups A,B,C)											X	X	X	X	X	X					
Complete sustainability assessment														X							
Analyze data															X	X	X				
Submit progress reports						X						X						X			X
Disseminate & submit manuscripts																			X	X	X

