**Methods:**

The purpose of this project is to test innovative hearing health education programs delivered to a large target group and to determine the effectiveness and sustainability of these programs in promoting hearing health among farm and rural youth. Specifically, this project includes: a) an interactive face-to-face informational program alone, b) an interactive face-to-face informational program followed by an Internet-based booster, and c) a no-intervention control. Sites will include selected affiliates of a major farm youth safety education organization. Data will be collected at baseline, 3, and 12 months. A linear mixed model will be used to compare the effectiveness of the three interventions over time. Descriptive statistics will be used to compare program costs and sustainability ratings.

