#### Retention

With parental consent, youth will select their preferred communication media (telephone, postal, email), which will be used to communicate study activity reminders and surveys. The study coordinator will distribute reminders, and 3- and 12-month follow-up surveys by email, postal mail, or phone. Coordinators will access youth for 12 month follow-up as they return for Safety Day participation in the subsequent yearly meeting. The study team will support the PAF Safety Day trainers, coordinators, and instructors through site visits and frequent email and telephone contacts. Participating youth will be recognized with a $5 cash incentive for completing up to three (depending on study arm) surveys. Coordinators will be awarded checks on submission of study materials (surveys) as tokens of appreciation for their contribution to accomplishment of study goals (e.g., completion of training, coordination, & teaching; responding to survey requests).

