The primary measure to assess effectiveness is the 6 item scale of intention to use hearing conservation strategies (including turning down the volume, moving away from the noise, and using hearing protection devices such as ear plugs). The knowledge scale and the scale of interpersonal influences will also be examined. All individuals will be asked to assess these measures before intervention (baseline), and at 3 months and 12 months after the intervention. Since the cluster randomized design will be used to assign interventions and repeated measurements will be collected from the same individuals, linear mixed effects model will be used to investigate the effect of the interventions. The outcome variable is the scale of intention to use hearing conservation strategies. The important/main fixed effect is a categorical variable identifying the type of interventions. In addition, demographics variables will be included in the mixed model as fixed effects to increase the precision of estimates. The random effect in the model is the *site* variable. More precisely, we will use random intercept model for the *site* variable. We assume the site variable follows a normal distribution with mean zero and is independent to the error terms in the mixed model. The hypothesis is that there will be a significant effect of hearing intervention on the use of hearing conservation strategies and the intervention group will have higher use of hearing conservation strategies than the control group. If the effect of intervention is significant, follow up descriptive statistics on mean intent by time by treatment group will allow us to describe the effects, for example to determine whether each treatment led to more improvement in intent to use than the control condition and how big those effects were. Further tests within this analysis will compare the effects of the two interactive hearing interventions on youth.

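### The timetable gives the 3-month survey to Groups A and B only, while the analysis text has all three arms measured at 3 months; the two must be reconciled

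*Protocol article*

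**What the plan says.** Table 2, placed under Intervention effectiveness evaluation, has the row "Distribute, collect 3-month surveys (Groups A,B"). The 12-month row of the same table reads "Collect 12-month surveys; distribute incentives (Groups A,B,C"). The Retention section offers youth an incentive "for completing up to three (depending on study arm) surveys".

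The Statistical analysis section states: "All individuals will be asked to assess these measures before intervention (baseline), and at 3 months and 12 months after the intervention". The Abstract, under Methods, gives the same schedule with no restriction by arm: "Data will be collected at baseline, 3, and 12 months". It adds: "A linear mixed model will be used to compare the effectiveness of the three interventions over time". For Aim 1, the Statistical analysis section plans that "follow up descriptive statistics on mean intent by time by treatment group will allow us to describe the effects", including whether each treatment improved intent more than the control condition did.

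The Interventions section places the Internet booster after completion of the 3-month survey.

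**The concern.** The article gives two incompatible measurement schedules for the control arm. Site staff working from the timetable would not survey Group C at 3 months, and that wave cannot be collected later. The analyst working from the Statistical analysis section would expect those data, because the by-time description of each treatment against control needs a control mean at each time.

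At stake is the 3-month comparison with control, which is one of only two follow-up waves. Without Group C, what remains at 3 months is change from baseline in Groups A and B on a self-reported outcome. The article itself says, under Self-reported measures, that such outcomes are open to social desirability bias. The arms would also differ in how often they were surveyed before month 12.

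**Working it through.** **1. The passages side by side**

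| Place | Group C at 3 months? |
|---|---|
| Table 2, 3-month row | No: A and B only |
| Table 2, 12-month row | Names A, B and C |
| Retention, incentive sentence | Number of surveys depends on arm |
| Retention, survey distribution sentence | 3- and 12-month surveys, no arm excluded |
| Statistical analysis | Yes: all individuals |
| Abstract, Methods | No arm restriction |

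Table 2 writes A,B,C where it means all arms (the 12-month row, and the distribution of materials), so the shorter label in the 3-month row does not look accidental. The incentive sentence points the same way. If every youth had three scheduled surveys, the number would not depend on arm.

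**2. The plan's own figure, reproduced**

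Inputs from Power and sample size justification: 36 sites split equally over 3 arms (12 each), 16 youth per site, d = 0.48, ICC = 0.10, two-sided alpha 0.05.

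- Enrollment: 36 × 16 = 576, or 576/3 = 192 per arm.
- Design effect: 1 + (16 − 1) × 0.10 = 2.5.
- Effective size per arm: 192/2.5 = 76.8.
- Noncentrality: 0.48/√(2/76.8) = 2.974.
- Power, noncentral t with 12 + 12 − 2 = 22 df: 0.811, against the stated 80%. The normal approximation gives 0.845.

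The stated power is therefore for one intervention arm against control, 12 v 12 sites.

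**3. Observations under each schedule**

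- Statistical analysis section: 3 waves × 576 = 1,728.
- Table 2, taking baseline as collected in all arms: 576 + 384 + 576 = 1,536.
- Difference: 192, which is the whole of the control arm's 3-month wave (192 planned against 0).

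**4. What the 3-month wave can show**

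According to the Interventions section, the booster follows the 3-month survey. Table 2 agrees: the first 3-month surveys fall in months 9/10 and the first booster reminders in months 13/14. Groups A and B have thus had the same treatment at 3 months, and a contrast between them carries no treatment difference.

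**5. What is available at 3 months if Group C is surveyed**

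Using the same inputs and method. The second column assumes 20% loss from 16 per site.

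| 3-month contrast | 16 analysed per site | 12.8 analysed per site |
|---|---|---|
| One intervention v C (12 v 12 sites) | 0.81 | 0.78 |
| A and B pooled v C (24 v 12 sites) | 0.92 | 0.89 |

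Under Table 2 as written, neither contrast can be estimated from observed data.

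**The case against.** The best defence is that Table 2 is a project timetable of activities and benchmarks, not an assessment schedule, and that its arm labels are loose. The row that includes baseline data collection also ends in Groups A,B. Read literally, it would drop Group C at baseline, which nobody intends. On this view the Statistical analysis section governs and Table 2 is what needs correcting. That is possible, and it means the loss of the 3-month comparison is conditional. It does not remove the conflict. The label in the baseline row can apply to program delivery alone, whereas the 3-month row contains nothing but the survey, and the incentive sentence supports the table.

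A reader might infer three further harms. The article does not support them as stated.

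- **Imputation would pull the 3-month effect toward zero.** The missing-data section plans one imputation model, based on baseline data, for all three conditions. It addresses missing data under the heading of response rate and retention, and does not say that a wave never scheduled for an arm would be imputed. If it were, the model could draw only on Groups A and B and could not recover the control mean. That is a reason to rule it out in the text, not a consequence already fixed.
- **Unequal waves would bias the mixed model.** This needs a model without a time term. The Statistical analysis section names its main fixed effect without claiming a full list, and the Abstract speaks of comparison over time. A time effect would absorb a shift common to all arms. This harm and the imputation harm also rest on different treatments of the same missing values, so they cannot be added together.
- **The 12-month contrast is confounded with repeated testing.** One extra short survey could matter, but nothing in the article allows its effect to be sized.

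**Conclusion.** The contradiction is real. Table 2 and the incentive sentence in Retention conflict with the Statistical analysis section and the Abstract on whether Group C is surveyed at 3 months. If Table 2 is followed, Group C has 0 of 192 planned 3-month observations, and no comparison of either intervention with control can be made at that wave from observed data. Because Groups A and B are alike in treatment up to then, no other informative comparison exists at 3 months.

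This rests on two assumptions: that the timetable is what sites would carry out, and that the booster follows the 3-month survey as the Interventions section says. One sentence under Intervention effectiveness evaluation can be read as placing both post-tests after the booster, and it should be aligned at the same time.

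It would go too far to say that the trial has no control comparison at 3 months, since the analysis text plans one. It would also go too far to say that the primary comparison is lost. No time point is named as primary, and the randomized 12-month comparison with control stands under either schedule. The extra survey contact in Groups A and B is a possible influence on it, of unknown size.

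**What to change.** **Preferred.** Add Group C to the 3-month survey row of Table 2. Reword the Retention section so that all arms have the same three surveys and the same incentive terms. The cost is up to 192 more short surveys with their reminders. If the $5 is paid per survey, that adds up to 192 × $5 = $960; if it is a single payment covering all surveys, no incentive cost is added. The change has to be made before the 3-month surveys go out.

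**If Group C cannot be surveyed at 3 months.** Correct the Abstract and the Statistical analysis section to say that Group C has no 3-month data. Make no 3-month comparison with control. State under Response rate, retention, and missing data that Group C 3-month values are not imputed. Name 12 months as the randomized comparison with control. This costs only a text correction, but it gives up the 3-month comparison with control and leaves the arms with unequal survey contact before month 12.

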#### Use of hearing conservation strategies

The 3-item, multiple-choice instrument measures youths’ use of hearing conservation strategies (i.e., turn it down, walk away, use protection) during the previous 3-months. The instrument has a reading grade level of 6.9. A sample item from this instrument is, “During the past 3 months, how often did you wear earplugs or ear muffs when you were around loud sound?”

#### Intent to use hearing conservation strategies

The 6-item, multiple-choice instrument measuring youths’ intent to use hearing conservation strategies [28]. The instrument has a reading grade level of 5.6. A sample item from this instrument is, “*If earplugs were around when I needed them, I would use them*.”

#### Knowledge of hearing health

The 12-item, multiple-choice instrument to measure youths’ knowledge of noise, its effects on hearing, and hearing conservation strategies was adopted from items used by Martin et al. to measure this concept among elementary students [28]. A sample item from this scale is, “Which sounds can be loud enough to damage your hearing?”

#### Interpersonal factors influencing use of hearing conservation strategies

The 1-item, multiple-choice instrument to measure interpersonal factors influencing use of hearing conservation strategies among youth was adopted from a set of items used by Martin et al [28]. The item queries, “Wearing earplugs around your friends (if no one else is wearing them) would be (*very* to *not at all embarrassing*).” The instrument has a reading grade level somewhat higher (11.3) than the other instruments, due to use of the parenthetical phrase “*if no one else is wearing them*” and the multi-syllabic word, *embarrassing.* However, in previous use and pretesting, 4th grade students responded to this item without difficulty.

#### Process evaluation

Measurement of program process will include program fidelity, dose delivered, dose received, reach, recruitment, and context using instruments designed by the interdisciplinary study team for this purpose. The process evaluation plan was developed with consideration to system resources and program characteristics and context. Sample measurement items for the interactive Safety Day program follow. Fidelity will be measured by research team review of lesson audiorecordings for key points. Group C (control) site instructors will respond to a survey querying the inclusion of hearing conservation messages within the context of their sessions not specific to this topic (e.g., tractor safety). Dose of Intervention 1 will be measured using an instructor survey item, “How many minutes were spent on the lesson with each group of learners?” *Dose of intervention 2* will be measured as youth log into the DDVE site where they will enter identifying information which will allow for their time on the DDVE Web site to be tracked. Consistent with standard dose measurement methods, inactive time on site will result in stopping the time-on-site clock. The study team will monitor local Safety Day coordinators and instructors using phone calls and email messages timed to coincide with program planning, delivery, and follow-up to support delivery of the intervention as planned, and to accomplish submission of post-intervention surveys. *Reach* will be measured by counting the number of Safety Day youth (by site) who received the hearing health lesson. *Recruitment* will be measured using a coordinator survey item, “List and describe the youth recruitment procedures used.” *Context* includes the organizational factors, barriers, and facilitators to program delivery. Context will be measured using coordinator and instructor survey items, “What were the barriers to implementing the lesson?” and,”What were the facilitators to implementing the lesson?”

#### Demographics

This 3-item instrument measures youths’ sex, age, and race/ethnicity.

#### Cost

The cost of implementing the program will be based on data associated with program personnel, instructional materials, and travel incurred with the educational process.Personnel (coordinators, instructors, youth): We will estimate hearing education program personnel costs beyond those already incurred through previously established Safety Day programs, i.e., youth, coordinator, and instructor time.Instructional materials: We will value all materials used to implement the lesson (e.g., sound meters, printed supplies), including lesson development costs and youth time on public-access or home-based computers.Travel: We will estimate travel costs incurred by coordinators, instructors, and youth to participate in pre-program training and the local Safety Day program.

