### Interventions

The study aims to test alternative hearing health education programs, and determine their effectiveness and sustainability for farm and rural youth.

Intervention A consists of the interactive face-to-face hearing conservation program developed by the project team. It consists of discovery-based, developmentally appropriate activities designed to teach common farm and recreational sources of hazardous noise, effects of hazardous noise on ear structure and function, and age-appropriate ways to protect oneself, e.g., walk away, turn it down, and wear protection. The 20-minute lesson includes student involvement in demonstrations and visuals, demonstration and supervised practice in insertion of a child-safe hearing protection device, provision of a sample hearing protector, and elements relevant to the rural and farm community (e.g., common farm noise sources). In a preliminary test with 64 fourth grade students, comparison of pre- and post-test results showed changes of scores in the desired direction, and pre-post-test differences were statistically significant*.* In addition, results of the pilot test suggested that overall, the pilot program was acceptable to school officials and students, instruments were reliable and valid, and the brief educational program is feasible.

Training in use of the face-to-face hearing health lesson plan will be provided to selected local safety program coordinators through face-to-face and virtual train-the-trainer sessions conducted by study personnel, and a written lesson plan; the Study Coordinator will also reach out to instructors by offering individualized training and consultation. Coordinators will prepare instructors, include the lesson in their local program, and complete surveys. The hearing health lesson includes use of easily accessible teaching materials, e.g., paper-based visual aids, locally-sourced noisy equipment (e.g. electric leaf blower), pipe cleaners, and a sound meter.

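### Program cost leaves out the study staff who train Group A and B sites and send Group B's booster reminders, so Aim 2 understates incremental cost by an amount the article does not let one compute

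*Protocol article*

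**What the plan says.** All references are to the protocol article.

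- **Cost, personnel.** The category is set out as "Personnel (coordinators, instructors, youth): We will estimate hearing education program personnel costs", and its scope is the increment "beyond those already incurred through previously established Safety Day programs, i.e., youth, coordinator, and instructor time".
- **Cost, materials.** All lesson materials are valued, "including lesson development costs and youth time on public-access or home-based computers".
- **Cost, travel.** The same three groups appear again: "We will estimate travel costs incurred by coordinators, instructors, and youth to participate in pre-program training and the local Safety Day program".
- **Aim 2 (Statistical analysis).** Dollar costs are summarised by site, with materials and travel as examples. Time costs are those of volunteers and students. Site-level costs are compared across the three arms by one-way analysis of variance, and a cost-effectiveness ratio follows if the intervention effect is significant.
- **Interventions.** Site coordinators are prepared through "face-to-face and virtual train-the-trainer sessions conducted by study personnel", and the Study Coordinator also offers instructors individual training and consultation.
- **Retention.** "The study coordinator will distribute reminders, and 3- and 12-month follow-up surveys by email, postal mail, or phone".
- **Table 2 (under Intervention effectiveness evaluation).** Coordinator training is listed for Groups A and B. A separate row, in months 13 to 24, reads "Distribute booster reminders (Group B").

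**The concern.** The personnel list is closed: it is introduced by i.e., and the category label, the travel line and the Aim 2 time costs leave the same people out. The coordinators on it are the local Safety Day coordinators (36, one per site, in Power and sample size justification). The Study Coordinator is a different person, named separately. Two recurring pieces of delivery work, training the sites and reminding Group B youth to use the booster, are therefore done by people whose time enters no cost line.

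Aim 2 exists to compare what the programs cost. The Discussion says the trial is to determine the most cost-effective and sustainable approach, and Dissemination foresees full-scale use within Safety Day. If part of the delivery labour is missing, both active programs look cheaper against no intervention than they are, and adding the booster looks cheaper than it is. Any ratio built on those differences is too favourable.

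**Working it through.** The article states no cost, wage, staff-hour or reminder count, so there is no figure to reproduce. The check sets each delivery component against the cost lines.

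| Component | Who supplies it | Arms | Counted? |
|---|---|---|---|
| Lesson development | Project team | A, B | Yes (materials) |
| Travel to training | Coordinators, instructors, youth | A, B | Yes (travel) |
| Training and consultation | Study personnel, Study Coordinator | A, B | **No** |
| Teaching and local coordination | Instructors, local coordinators | A, B | Yes (personnel) |
| Youth time, including computer time for the booster | Youth | B for the booster | Yes (personnel, materials) |
| Booster reminders | Study coordinator | B | **No** |
| Time-on-site tracking | Study | B | No, but this is dose measurement |

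**Effect on each contrast.** Let T be the mean uncounted training and consultation cost per site in A and B, and R the mean uncounted booster-reminder cost per Group B site. Full cost minus counted cost is T in A, T + R in B, and 0 in C. Hence:

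- A minus C is understated by T.
- B minus C is understated by T, plus R.
- B minus A is understated by (T + R) − T = R, if training effort per site is about equal in A and B. Table 2 gives both arms the same training row.

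**Effect on the ratio.** With a positive effect difference, the counted ratio equals the full ratio times counted/(counted + omitted). The relative understatement is the omitted share of the full incremental cost.

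**Can R be sized?** Not from the article. From Power and sample size justification, 36/3 = 12 sites per arm and 12 × 16 = 192 Group B youth. The remaining inputs are assumptions:

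- Omitted: 1 to 3 reminders at 5 to 15 staff minutes each. Low: 192 × 1 × 5/60 = 16 h. High: 192 × 3 × 15/60 = 144 h. Per site: 16/12 = 1.3 h to 144/12 = 12 h.
- Counted: 15 to 60 minutes of booster use per youth. Low: 192 × 15/60 = 48 h. High: 192 × 60/60 = 192 h. Per site: 4 to 16 h.

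The lower figure for reminders is not a true floor: Retention allows email, and batch email could take much less. So R may be trivial or comparable with the youth time counted. T cannot be sized at all, since no session length or number is given.

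**The case against.** A reader might infer that the booster is costed at almost nothing against Group A. The article does not support that. Youth time on computers is expressly valued, the booster is a self-paced youth activity whose main resource is that time, and Process evaluation logs it. The inference has some basis only for a dollars-only summary, because the exhibit is free to use and Aim 2 summarises student time separately. Nor can the training omission make the booster look cheap, since it is common to A and B.

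Other points on the other side:

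- **Some staff work is research, not delivery.** Log-in and time-on-site tracking measure dose, and the reminder sentence under Retention also covers the follow-up surveys. This stands. Only the booster-reminder row in Table 2 is clearly specific to Group B's program.
- **Incremental cost over existing Safety Day programs is a legitimate perspective.** The article also says, under Theoretical framework, that training is already a Safety Day activity which the study increases. How much of the study's training an adopter would have to buy is therefore unknown. But no perspective is stated that would explain the exclusion, and counting lesson development, a project-team input, sits badly with leaving out the same team's recurring delivery work.
- **A journal article leaves costing detail to the full protocol.** That would answer silence. Here the article states a closed list.
- **Aim 2 is not the primary aim, and the ratio is conditional.** True. This limits the consequence, not the error.

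**Conclusion.** The point holds in a limited form. As written, program cost excludes study-staff training and consultation time for A and B and booster-reminder time for B. Both active arms are understated against C, and B is understated against A by the reminder time only. The sign follows from the cost definition and the division of labour. The cancellation in B versus A assumes similar training effort per site in the two arms.

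The size is undetermined. The hours shown for reminders rest on assumed counts and minutes, and nothing in the article shows that an Aim 2 conclusion would change. The effectiveness analysis is unaffected.

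**What to change.** Add study-staff delivery time to the personnel category in Cost and to the time costs in Aim 2:

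- training and consultation time for Groups A and B;
- booster-reminder time for Group B.

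Exclude surveys, retention contacts, dose tracking and other research tasks. Log the time prospectively, because it is hard to reconstruct later. Record it by site, apportioning shared sessions and batch mailings by a stated rule, since the cost comparison is at site level.

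Report the incremental costs A minus C, B minus C and B minus A, and the cost-effectiveness ratio, with and without these lines. The reader can then see how far the result depends on them.

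The cost is a simple time log kept by existing staff. The downside is that A and B will appear somewhat more expensive.
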